#### Secondary study parameters

Our secondary objectives include a comprehensive evaluation of various cognitive domains, extending beyond the primary focus on verbal memory. The LDST serves as a metric for assessing visual scanning, mental flexibility, sustained attention, psychomotor speed, and speed of information processing. The LDST outcomes include the total number of correct written items after 90 s, and the total number of correct items read after 90 s. The TMT measures visual attention (Part A) executive functioning and mental flexibility (Part B). The TMT outcome is the time (in seconds) required to complete each part individually (Part A and Part B). Spatial memory is measured by the spatial pattern separation task, evaluating participants’ accuracy in identifying the position of objects on a computer screen. The ADAS-Cog will be used as it measures language and memory in general. Subtests within the ADAS-Cog encompass naming objects and fingers, following commands, constructional praxis, ideational praxis, orientation, remembering test directions, spoken language, comprehension, and word-finding difficulty. The total score of the subtests is utilized as the ADAS-Cog. The word recall task and the word recognition task have been removed from the task, to avoid interference with our primary outcome measure (15-VLT). The 15-VLT recognition task is part of the secondary outcomes. The MMSE serves as a screening tool for general cognitive impairment, with the total score acting as the MMSE outcome. Confrontational naming is assessed through the Shortened BNT-15, with the total score derived from correctly named items, either spontaneously or after semantic cues.

Furthermore, our secondary objectives extend beyond cognitive assessments to include well-being and quality of life questionnaires for both participants (QoL-AD, EQ-5D, HADS) and their (informal) caregiver (NPI, ADCS-ADL). The outcome measure of the EuroQol, the QoL-AD, and the ADCS-ADL is the total score. The outcome measure of the HADS is the total score, as well as sub-scores for depression and anxiety separately. The outcome of the NPI is the total care score (frequency × severity) and total burden score. Suicidal intent and thoughts about suicide are explored using item 9 of the Beck Depression Inventory 2 (BDI-2). For all secondary outcomes, the change from baseline to acute effects, change from baseline to 3 months, change from baseline to 6 months, and 6 months to follow-up will be statistically analysed.

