Individuals undergoing current irradiation are excluded from the study as irradiation can cause radiation-induced cognitive impairment. Individuals who have a Fazekas score of 3 and higher on MRI scans are excluded as it indicates a mixed (AD and vascular) or vascular origin of cognitive impairment. Individuals with chronic viral infections (human immunodeficiency virus, and hepatitis B and C) are excluded from the study due to the possible risk of treatment-related toxicity. Normal pressure hydrocephalus (NPH), Morbus Huntington, Parkinson’s disease, recent transient ischemic attack (TIA), or cerebrovascular accident (CVA) within the last 2 years, TIA/CVA followed by a cognitive decline within 3 months are all exclusion criteria because of the cognitive impairment related to these disorders. COPD (gold criteria 3 and 4) are exclusion criteria due to the medication used in this study trial and its original indication. Roflumilast is a possible add-on treatment for COPD and severe asthma. Accordingly, although the dosage in this study is substantially lower than usually is prescribed in COPD patients (250 or 500 μg), we want to avoid cognitive improvement due to the improvement of any COPD-related symptoms. A lifetime history of schizophrenia, bipolar disorder, or psychotic symptoms not otherwise specified, current affective disorder (anxiety or major depression), cognitive problems due to alcohol abuse, brain tumours, epilepsy, and encephalitis are exclusion criteria because of the possible (temporary) cognitive impairment associated with these disorders. Other exclusion criteria are current treatment with (or other use of) cannabis, opiates, benzodiazepines, methylenedioxymethamphetamine, and cocaine. The use of medications strongly inhibiting CYP3A4 or CYP1A2 is also an exclusion criterion because of the interference with roflumilast metabolism resulting in the reduced therapeutic effectiveness of roflumilast. Individuals with rare hereditary problems of galactose intolerance, Lapp lactase deficiency, or glucose-galactose malabsorption will be excluded, as both the placebo and roflumilast contain lactose monohydrate. Moreover, participants are not allowed to participate in other drug trials during the study period. Lastly, participants unable to be accompanied at every test session by the same (informal) caregiver will be excluded. Roflumilast is contraindicated in individuals with moderate to severe liver impairment (e.g. Child–Pugh B and C) and those with hypersensitivity to the active substance or any of the listed excipients, namely, lactose monohydrate, corn starch, povidone, and magnesium stearate, will also be excluded from the study.

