#### Other outcomes

We aim to conduct a pharmacokinetic validation of roflumilast and its active metabolite roflumilast N-Oxide in blood plasma at T1 (acute test day), T2 (3-month test day), and T3 (6-month test day). As this is the first study to investigate a dose of 50 μg of roflumilast, a previous pharmacokinetic validation has never been performed for this dose specifically. Considering the inverted U-shaped dose–response curve, we expect 50 μg to reach the same effectiveness as 100 μg by likely achieving similar plasma levels after chronic administration. The outcome should determine approximately the same plasma level of roflumilast and its active metabolite per participant at measurements T2 (3 months) and T3 (6 months) if the participant complied with study medication adherence. We expect participants who were allocated in the 50 μg condition to have lower plasma levels than participants who were allocated in the 100 μg condition at the acute measurement. At the beginning of participation, participants will be required to complete a concise questionnaire, capturing essential demographic and lifestyle variables. This includes the date of birth, age, sex, highest education completed, civic status, living situation, housing situation, ethnicity, height, weight, amount of smoking per day, average alcohol intake per week, relationship with the (informal) caregiver, and any positive family history pertaining dementia, Parkinson’s disease, or amyotrophic lateral sclerosis. Upon study completion, a follow-up assessment will be conducted to identify any changes in the aforementioned variables. In addition to these demographic aspects, tau in tear fluid will be measured. Based on the current literature, it is possible to measure tau in tear fluid [22]. Our study aims to discern whether roflumilast induces changes in tau concentrations within tear fluid. The statistical analysis will focus on changes from baseline to the 6-month mark. Furthermore, vigilant monitoring of adverse events (AEs) and serious adverse events [25] will be integral to our study.

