### Sample size {14}

Following a previous study demonstrating an estimated effect size of 0.69 (Cohen’s *d*) in healthy elderly and individuals with pronounced age-associated memory impairment [16], a power calculation for *F*-tests has been performed. This results in group sizes of 24 participants per group (Power 0.8; alpha 0.05), in consideration of potential dropout rates observed in the previous study, wherein nearly 10% of the participants withdrew for reasons unrelated to drug effects. To mitigate potential attrition, an additional 3 participants per treatment group will be included, resulting in 27 participants per group.

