### Statistical methods

#### Statistical methods for primary and secondary outcomes {20a}

Descriptive statistics for continuous parameters will include sample sizes, means and standard errors of the dependent variables, and covariates for each distinct level combination of factors. For categorical data, summary tables will present counts and percentages. Statistical summaries will be presented by treatment, sequence, or period. The repeated measures, namely the outcome variables of the cognitive assessments and the subjective well-being-related scales, will be analysed using mixed models. The between-subject factor will be the treatment group (three levels: placebo, 50 μg roflumilast, and 100 μg roflumilast). The scores of each task will be entered as the within-subject factor, as well as time (T1, i.e. acute, T2, i.e. 12 weeks, T3, i.e. 24 weeks, T4, i.e. 2-week follow-up). An additional interaction term between the treatment group and time is included to determine whether the different treatment groups will lead to different trajectories over time. Subject covariates included will be sex, age, and education. Additionally, at the end of the study, we will ask each participant which intervention arm they think they have received (placebo, 50 mcg roflumilast, or 100 mcg roflumilast). Because of exclusion and inclusion criteria related to the patient recruitment of the study, the population recruited will be homogenous. Note that groups will not be able to be matched because of the applied randomization block strategy. The significance level will be set at *a* = 0.05.

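### The suicidality item (BDI-2 item 9) falls under the tested change-from-baseline rule for all secondary outcomes, which suits a rare single-item safety signal poorly

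*Protocol article*

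**What the plan says.** The Secondary study parameters part of Outcomes {12} in the protocol article lists the participant and caregiver questionnaires and then adds: "Suicidal intent and thoughts about suicide are explored using item 9 of the Beck Depression Inventory 2 (BDI-2"). For the EuroQol, QoL-AD, ADCS-ADL, HADS and NPI it names the score that serves as the outcome. For item 9 it names no score, cut-off or case definition.

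The sentence that follows sets the analysis: "For all secondary outcomes, the change from baseline to acute effects, change from baseline to 3 months, change from baseline to 6 months", and then 6 months to follow-up, are to be statistically analysed. Item 9 is not exempted.

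Statistical methods {20a} says that the repeated measures, "namely the outcome variables of the cognitive assessments and the subjective well-being-related scales, will be analysed using mixed models", with group, time and their interaction, at a significance level of 0.05. Item 9 is not named there.

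Harms are described elsewhere. Other outcomes promises "vigilant monitoring of adverse events (AEs") and of serious adverse events. Adverse event reporting and harms {22} covers events reported spontaneously or observed by staff. Neither section mentions item 9. Section {21a} states that there is no data monitoring committee.

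**The concern.** For a suicidality item, what matters is whether any participant newly reports such thoughts or intent, how many do so, and on which arm. A mean change per arm does not answer that.

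Eligibility criteria {10} excludes "current affective disorder (anxiety or major depression"), so most participants will probably score zero at baseline. One or two new cases then move the arm mean only slightly, and a test on that mean has little power. Where some participants are positive at baseline and improve, their improvement is subtracted from the new cases.

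At stake is how the result is summarised. If the stated rule is followed, a few new cases on an active arm could appear only as a non-significant mean change. Without a data monitoring committee, the by-arm safety summary carries more weight.

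**Working it through.** The article gives no rate, power or sample size for item 9, so there is no figure of its own to reproduce. The check asks what the stated rule would show for a small number of new cases.

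**Inputs from the article**
- Enrolled per arm: 27; evaluable per arm: 24 (Sample size {14}).
- Significance level: 0.05 (Statistical methods {20a}). The sidedness is not stated, so two-sided is assumed.

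**Assumptions not in the article**
- The item is ordinal and each change is one point.
- Placebo is unchanged.
- For the power figures: placebo onset 1%, active-arm onset 5% or 10%, baseline prevalence 0 to 10%, and half of baseline positives resolving.

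**Dilution (everyone starts at zero).** With k new cases among n on one active arm:
- mean change = k/n
- variance of change s² = k(n − k) / [n(n − 1)]
- two-arm t = (k/n) / √(s²/n), on 2n − 2 degrees of freedom (the placebo variance is 0, so equal weighting of the two arms leaves s²/n)
- if variance is pooled over three arms with the third also unchanged, the standard error is √[(s²/3)(2/n)], on 3n − 3 degrees of freedom

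For n = 27 and k = 3: mean = 3/27 = 0.111 and s² = 3 × 24 / (27 × 26) = 0.1026.
- Two arms: standard error = √(0.1026/27) = 0.0616, t = 1.80, p = 0.077.
- Three arms pooled: standard error = √(0.0342 × 2/27) = 0.0503, t = 2.21, p = 0.030.

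| New cases, active vs placebo (27 per arm) | Mean change | p, two-arm t-test | p, pooled over three arms |
|---|---|---|---|
| 2 vs 0 | 0.074 | 0.155 | 0.081 |
| 3 vs 0 | 0.111 | 0.077 | 0.030 |
| 4 vs 0 | 0.148 | 0.038 | 0.011 |
| 5 vs 0 | 0.185 | 0.019 | 0.004 |

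With 24 per arm the two-arm values for 2, 3 and 4 cases are 0.155, 0.076 and 0.037. All these p-values are approximate for so sparse an item.

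**Offsetting (some participants positive at baseline).** With 24 or 27 per arm, 3 new and 3 resolved cases give a mean change of (3 − 3)/n = 0 and p = 1.00 against an unchanged placebo arm. With 3 new and 2 resolved, the mean is 1/24 = 0.042 or 1/27 = 0.037, and p = 0.66. This needs baseline-positive participants who improve.

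**Counting compared with testing.** The chance of at least one new case among 24 is 1 − (1 − q)²⁴. For q = 5% it is 1 − 0.95²⁴ = 0.71; for q = 10% it is 1 − 0.90²⁴ = 0.92. Simulated power of the two-arm change-score test with 24 per arm is about 0.02 to 0.05 at 5% onset and 0.13 to 0.17 at 10%. A count would usually show a case where the test would not reach significance.

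**A test on the counts does not help.** Fisher's exact test with 27 per arm gives p = 0.24 for 3 against 0 and 0.051 for 5 against 0. The counts therefore need to be reported descriptively.

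**The case against.** The strongest reply is that the article does not commit to modelling item 9. The item is only explored, it has no named outcome score, the Objectives section does not list the BDI-2, and the mixed-model sentence does not name it. Safety information also arrives by other routes: adverse-event recording, expedited reporting of serious events, annual safety reports, regular calls and an available research physician. Nothing prevents a positive answer from being recorded as an adverse event, and {20a} promises counts and percentages for categorical data. Safety tables and listings commonly belong in the full protocol or the analysis plan, which are not shown.

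Much of this stands. It limits the consequences and rules out some stronger readings that a reader might infer:
- **That offsetting is the main danger.** It needs baseline-positive participants, and the exclusion of current affective disorder probably makes them few. Dilution is the main mechanism.
- **That up to five new cases against none would pass as non-significant.** That holds only for Fisher's test at 27 per arm, which the article does not plan. On a change score, four against none already gives p of about 0.04 in two arms.
- **That a harm signal would be missed, or that the item is labelled an efficacy outcome.** The article says neither, and the parallel safety routes argue against the first.

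The reply does not remove the explicit rule. It covers all secondary outcomes, directly follows the sentence on item 9 and makes no exception. That is a stated choice and not a detail left to another document.

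**Conclusion.** The point holds as a problem with a stated rule. Item 9 sits among the secondary parameters, falls under a tested change from baseline, and has no stated link to the harms section. For a single item that is probably zero for most participants, that analysis answers the wrong question.

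The effect is limited. Two new cases on one active arm against none on placebo would not reach 0.05 under either variance assumption. Three would be borderline: about 0.08 with two arms and 0.03 with variance pooled over three. Four or more would reach 0.05. A small signal could therefore be summarised as no significant change, but need not be.

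This rests on one-point shifts, an unchanged placebo arm, two-sided tests, 27 per arm and few baseline positives. The article gives no prevalence for the item, and its assessment schedule (Fig. 1) is not shown. Severity is low to moderate.

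**What to change.** Exempt BDI-2 item 9 from the change-from-baseline sentence in Secondary study parameters and define it as a safety outcome reported descriptively. For each arm, and each visit at which it is collected, give the number of participants with a new positive response and the number with a worsened response relative to baseline, with the number assessed as denominator. Add an individual listing, carry out no significance test, and present the table alongside the adverse-event data, with a cross-reference from section {22}.

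The cost is one sentence and one table. The item is already collected, so no extra assessment or sample-size change is needed.

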#### Other outcomes

We aim to conduct a pharmacokinetic validation of roflumilast and its active metabolite roflumilast N-Oxide in blood plasma at T1 (acute test day), T2 (3-month test day), and T3 (6-month test day). As this is the first study to investigate a dose of 50 μg of roflumilast, a previous pharmacokinetic validation has never been performed for this dose specifically. Considering the inverted U-shaped dose–response curve, we expect 50 μg to reach the same effectiveness as 100 μg by likely achieving similar plasma levels after chronic administration. The outcome should determine approximately the same plasma level of roflumilast and its active metabolite per participant at measurements T2 (3 months) and T3 (6 months) if the participant complied with study medication adherence. We expect participants who were allocated in the 50 μg condition to have lower plasma levels than participants who were allocated in the 100 μg condition at the acute measurement. At the beginning of participation, participants will be required to complete a concise questionnaire, capturing essential demographic and lifestyle variables. This includes the date of birth, age, sex, highest education completed, civic status, living situation, housing situation, ethnicity, height, weight, amount of smoking per day, average alcohol intake per week, relationship with the (informal) caregiver, and any positive family history pertaining dementia, Parkinson’s disease, or amyotrophic lateral sclerosis. Upon study completion, a follow-up assessment will be conducted to identify any changes in the aforementioned variables. In addition to these demographic aspects, tau in tear fluid will be measured. Based on the current literature, it is possible to measure tau in tear fluid [22]. Our study aims to discern whether roflumilast induces changes in tau concentrations within tear fluid. The statistical analysis will focus on changes from baseline to the 6-month mark. Furthermore, vigilant monitoring of adverse events (AEs) and serious adverse events [25] will be integral to our study.

### Participant timeline {13}

The current study consists of a medical screening, a baseline assessment, and subsequent acute, 12-week, 24-week, and 26-week follow-up test sessions. Figure 1 provides a detailed schedule of enrolment, interventions, and assessments. Preceding the medical screening, participants will receive a standardized medical questionnaire for completion at home. The voluntary submission of this questionnaire is encouraged to expedite the screening process. This questionnaire, solely intended for the research physician, will aid in determining eligibility criteria and does not constitute an outcome measure subject to statistical analysis. The screening will start with an explanation of the study, followed by signing the informed consent by the patient, the (informal) caregiver, and the researcher of the study. Subsequently, the MMSE, integral to inclusion criteria, will be administered. The medical screening will be performed by a research physician familiar with the study’s eligibility criteria. The first part of the medical screening involves an inquiry into the participants’ medical history through the medical questionnaire. Following, a physical examination will be performed, including checking appearance, extremities, skin, head, neck, eyes, ears, nose, throat, lungs, chest, heart, abdomen, and musculoskeletal system. Measurement of weight, height, systolic/diastolic blood pressure, and pulse rate will follow 5 min of rest in a supine position. Additionally, a resting 12-lead electrocardiogram will be recorded at a paper speed of 25 mm/s with at least 3 valuable beats per lead and a standard calibration (implying 1 mV = 10 mm for each lead). Blood samples (12 ml) will be collected for haematological and biochemical analyses. Urine samples will be processed for examination of urine status, urine sediment on indication, as well as a drug screening for cocaine, amphetamine, methamphetamine, marihuana, methadone, MDMA, morphine, barbiturate, and benzodiazepines. In instances where the 15-VLT and CDR scale data are unavailable, an assessment of these parameters will be conducted as part of the inclusion criteria. Participants with positive screening results will be invited for the baseline assessment. All visits have to be no more than 3 days after or before the set dates. Refer to Figs. 1 and 2 for a comprehensive overview of the study timeline and respective test days.

**Fig. 1 Fig1:**
[figure not shown]
Trial schedule. MMSE: Mini-Mental State Examination, 15-VLT: 15-word Verbal Learning Task, CDR: Clinical Dementia Rating, LDST: Letter Digit Substitution Task, ADAS-Cog: Alzheimer’s Disease Assessment Scale – Cognitive subscale, TMT: Trail Making Test, HADS: Hospital Anxiety Depression Scale, EQ-5D: EuroQol – 5 Dimensions, QoL-AD: Quality of Life Alzheimer’s Disease, NPI: Neuropsychiatric Inventory, ADCS-ADL: Alzheimer’s Disease Cooperative Study—Activities of Daily Living, ECG: Electrocardiogram, ROS: reactive oxygen species

**Fig. 2 Fig2:**
[figure not shown]
Schematic overview of test days

### Sample size {14}

Following a previous study demonstrating an estimated effect size of 0.69 (Cohen’s *d*) in healthy elderly and individuals with pronounced age-associated memory impairment [16], a power calculation for *F*-tests has been performed. This results in group sizes of 24 participants per group (Power 0.8; alpha 0.05), in consideration of potential dropout rates observed in the previous study, wherein nearly 10% of the participants withdrew for reasons unrelated to drug effects. To mitigate potential attrition, an additional 3 participants per treatment group will be included, resulting in 27 participants per group.

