Our secondary objectives encompass a comprehensive exploration of diverse cognitive domains. Included cognitive domains are as follows: mental speed/attention and executive functioning (Letter Digit Substitution Test (LDST) and Trail Making Test (TMT)), spatial memory (Spatial Pattern Separation Task), language (Alzheimer’s Disease Assessment Scale-Cognitive Subscale (ADAS-Cog), and the Shortened Boston Naming Test-15 (BNT-15)) and orientation (Mini-Mental State Examination (MMSE)) will be measured as well. In addition to cognitive assessments, we aim to gauge participants’ quality of life (Quality of Life AD (QoL-AD), EuroQol-5 Dimensions (EQ-5D)), psychological well-being (Hospital Anxiety Depression Scale; HADS), neuropsychiatric symptoms (Neuropsychiatric Inventory; NPI), and daily functioning (Alzheimer’s Disease Cooperative Activities of Daily Living Scale; ADCS-ADL). This multifaceted approach aims to illuminate the intricate interplay between cognition, quality of life, mood, and emotion. Outcome measures include a decrease in the reaction time (RT) in the LDST and TMT, as well as a decrease in errors in the LDST. Anticipated improvements encompass an increased total recognition score on the 15-VLT and an increased accuracy in all identified pattern completion scores of the pattern separation memory task. Total scores on the MMSE and ADAS-cog are expected to improve, as well as increased scores in well-being and quality of life, as indicated by the participant and the (informal) caregiver questionnaires. Furthermore, tau measurements from tear fluid samples will be assessed, as we speculate a potential positive impact of roflumilast on phosphorylated tau (pTau) concentrations [22]. Lastly, we will monitor the conversion from (a)MCI to dementia.

Three primary hypotheses have been formulated:The administration of 50 μg roflumilast over a chronic treatment period of 24 weeks, compared to placebo, is anticipated to improve episodic memory in participants with aMCI or mild AD dementia;The administration of 100 μg roflumilast over a chronic treatment period of 24 weeks, compared to placebo, is anticipated to improve episodic memory in participants with aMCI or mild AD dementia;The administration of 50 μg roflumilast over a chronic treatment period of 24 weeks, compared to 100 μg roflumilast, is anticipated to have comparable effects on episodic memory in participants with aMCI or mild AD dementia.

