### Trial design {8}

The ROMEMA study will be conducted according to a double-blind, randomized, placebo-controlled, superiority between-subjects design. The study includes a patient-based parallel group, with three arms (placebo, 50 μg roflumilast, and 100 μg roflumilast). Each arm comprises 27 participants, with randomization executed through block randomization, maintaining a balanced 1:1:1 allocation ratio.

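### The 24 per group for 80% power does not follow from d = 0.69 as stated, and 80% power is not shown for either dose-versus-placebo hypothesis

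*Protocol article*

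**What the plan says.** Sample size {14} takes an "estimated effect size of 0.69 (Cohen’s *d*) in healthy elderly and individuals with pronounced age-associated memory impairment" from an earlier study and says that "a power calculation for *F*-tests has been performed". It continues: "This results in group sizes of 24 participants per group (Power 0.8; alpha 0.05". It then notes that in the earlier study "nearly 10% of the participants withdrew for reasons unrelated to drug effects", so "an additional 3 participants per treatment group will be included, resulting in 27 participants per group". The section does not give the type of F-test, the value of Cohen's f, the number of measurements or any correlation.

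Trial design {8} describes three arms, "maintaining a balanced 1:1:1 allocation ratio". Objectives {7} lists three primary hypotheses. Two are superiority hypotheses, one for each dose: 24 weeks of roflumilast, "compared to placebo, is anticipated to improve episodic memory in participants with aMCI or mild AD dementia". The third expects the two doses to perform alike.

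Statistical methods {20a} plans a mixed model with treatment group, time (T1 to T4) and their interaction, with sex, age and education as covariates. Baseline 15-VLT is neither a listed covariate nor a listed time level. Outcomes {12} says that changes from baseline will be analysed.

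**The concern.** A reader will take "Power 0.8; alpha 0.05" as the power for the questions that the trial asks, namely whether each dose beats placebo after 24 weeks. There are two difficulties. The group size cannot be recovered from the effect size and test that are printed. And a three-arm F-test asks whether the arms differ at all, which answers neither pairwise hypothesis. If power per dose is well below 80%, a real effect of the assumed size would be missed more often than the one time in five that the stated figure implies. This matters because the article presents the study as the step before a possible phase III trial.

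**Working it through.** **Inputs.** d = 0.69, alpha 0.05, power 0.80, 24 and 27 per group (Sample size {14}); three equal arms (Trial design {8}). Sidedness is not stated, so two-sided is assumed, in line with a non-directional F-test.

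**Dropout step.** 24 / 0.9 = 26.7, rounded up to 27. This reproduces.

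**One-way three-arm F-test.** Noncentrality λ = N·f², with N = 72 and 2 and 69 degrees of freedom (critical F 3.13).

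| Conversion of d to f | f | λ | Power at 24 per arm | Per arm for 80% |
|---|---|---|---|---|
| d/2 | 0.345 | 8.57 | 72.9% | 29 |
| Means 0, d, d: f = d√2/3 | 0.325 | 7.62 | 67.5% | 32 |
| Means 0, d/2, d: f = d/√6 | 0.282 | 5.71 | 54.2% | 42 |

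None gives 24. The second row is the pattern that the three hypotheses imply.

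**One dose against placebo at one time point, no baseline adjustment.** Two-sided t-test with noncentrality d·√(n/2) and 2n − 2 degrees of freedom.

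- n = 24: 0.69 × √12 = 2.390, power 64.8% (65.4% with the error variance pooled over three arms)
- n = 27: 0.69 × √13.5 = 2.535, power 70.1%
- n = 34: 0.69 × √17 = 2.845, power 80.0%, so 34 per arm are needed
- d detectable with 80% power at n = 24: about 0.83

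**Variants that do land on 24.** These need inputs that the article does not give; the values below are assumptions. For a between-group F-test averaged over m measurements with common correlation ρ, λ = N·f²·k with k = m / [1 + (m − 1)ρ]. For adjustment by a baseline with correlation r, k = 1 / (1 − r²). The pairwise effect is then d·√k, tested as above with n = 24.

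| Variant | k | F-test power | d·√k | Pairwise power |
|---|---|---|---|---|
| Means 0, d, d; m = 2, ρ = 0.5 | 1.333 | 80.4% | 0.797 | 77.1% |
| Means 0, d, d; m = 3, ρ = 0.6 | 1.364 | 81.3% | 0.806 | 78.0% |
| f = d/2; m = 2, ρ = 0.7 | 1.176 | 80.1% | 0.748 | 71.8% |
| f = d/2; m = 4, ρ = 0.8 | 1.176 | 80.1% | 0.748 | 71.8% |
| f = d/2; baseline r = 0.4 | 1.190 | 80.5% | 0.753 | 72.3% |
| Means 0, d, d; baseline r = 0.5 | 1.333 | 80.4% | 0.797 | 77.1% |

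Pooling the error over three arms adds less than one point to the last column.

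**Baseline-adjusted comparison at 24 weeks with 24 per arm.** Effective effect d / √(1 − r²):

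- r = 0.5: 0.797, power 77%
- r = 0.6: 0.8625, power 83%
- r = 0.7: 0.966, power 91%

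**Sensitivity.** If alpha were split to 0.025 per dose, the unadjusted comparison would have 53% power at 24 per arm and need 42 per arm. The plan states no such split.

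**The case against.** The article says only that F-tests were used; it never says one-way. The planned analysis is a repeated-measures mixed model, so a repeated-measures power calculation is a natural reading, and ordinary values of m, ρ or r give exactly 24. A condensed article may leave those inputs to the full protocol. The 65% belongs to a two-sample test at one visit, which is not the planned analysis, and favourable inputs lift pairwise power above 80%: four measurements with ρ = 0.5 would give about 85%.

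Much of this stands. A reader might infer that no three-arm F-test on d = 0.69 can give 24, or that the trial simply has 65% power. The documents support neither. The first is disproved by the variants shown above. The second takes the power of an unadjusted single-visit test for that of the mixed model.

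Three things remain. First, the article prints a power figure, and that figure does not follow from what is printed with it. Second, the gains are not secured by the plan as written. An average over visits includes the acute test day and the follow-up after treatment, whereas the hypotheses concern 24 weeks of treatment. Baseline 15-VLT is not in the listed model. Analysing change from baseline gains nothing at a correlation of 0.5 (64.8% again), and gives about 74% at 0.6 and 86% at 0.7. Third, in each tabulated variant that explains 24, the pairwise power is still below 80%.

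**Conclusion.** The point holds in this form: 24 per group is not reproducible from the stated d = 0.69, and 80% power is not demonstrated for either dose-versus-placebo hypothesis. On the printed inputs alone, the omnibus F-test has 54% to 73% power and the unadjusted pairwise comparison about 65% (70% if all 27 per arm are evaluable). In the tabulated variants that reach 24, pairwise power is about 72% to 78%.

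The 65% rests on a two-sided 0.05 test, one time point and no baseline adjustment. The 72% to 78% rests on assumed values of m, ρ and r and on the first two conversions of d to f. The power of the planned mixed model cannot be settled from the article; it could be lower or higher than 80%, depending on correlations that are not given. This is therefore a power statement to be corrected and completed. It does not prove that the original calculation was wrong, and it does not show that the trial needs more patients.

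**What to change.** Restate Sample size {14} in three steps.

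1. Name the F-test actually used, with Cohen's f, the number of measurements and the correlation, so that 24 can be reproduced.
2. Report power for each dose-versus-placebo comparison at 24 weeks with 24 evaluable per arm: about 65% unadjusted (two-sided 0.05, d = 0.69), with 80% reached at d of about 0.83. Next to it, labelled as assumptions, give about 77%, 83% and 91% for baseline-to-24-week correlations of 0.5, 0.6 and 0.7 with baseline 15-VLT in the model.
3. If that higher power is to be claimed, add baseline 15-VLT to the primary model in Statistical methods {20a}.

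The figures at 0.025 per dose (53%; 42 per arm) belong in the text only as a sensitivity, unless an alpha split is adopted.

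The cost is a rewritten paragraph, one added covariate if step 3 is taken, and a less favourable headline power. No extra patients are needed.
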